### 9.4 MISSING VALUES

Missing values in primary and secondary outcome measures will be replaced by the last known value of any previous assessment (LOCF principle) for the primary analyses. Missing data for safety endpoints will not be replaced.

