The therapeutic relevance of targeting long-lived PCs in systemic autoimmunity initially derived from proof-of-principle studies demonstrating that the depletion of the autoreactive immunologic memory, including long-lived autoreactive PCs, in the context of high-dose chemotherapy followed by autologous hematopoietic stem cell transplantation, is a prerequisite for curative therapeutic approaches [26]. This concept further substantiated by studies with the proteasome inhibitor bortezomib, which depletes bone marrow plasma cells in a mouse model of SLE [27] and leads to clinical benefit with an associated reduction in autoantibodies and immunoglobulin levels in patients with refractory SLE [28]. Bortezomib treatment significantly reduced the number of PCs in peripheral blood and bone marrow, but their regeneration was fast. Within ten days of the last bortezomib injection, PC numbers significantly increased, accompanied by recurrence of anti-dsDNA antibodies [29]. Similar results have been obtained in our studies in murine lupus models, where combinatorial therapeutic strategies targeting PCs and their precursors with immunosuppression and/or B cell depletion resulted in sustained responses [22, 30]. Collectively, these data suggest that effective depletion of autoreactive long-lived plasma cells might be the key to effective treatment of SLE.

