## 5.3 ELIGIBILITY CRITERIA FOR LONG-TERM EXTENSION OBSERVATIONAL PERIOD

1. Participation in the DARALUP core-study
2. Written consent to the long-term extension of the observational period
3. If the patient is of childbearing potential, she agrees to: comply with effective contraceptive measures, has been using adequate contraception since the last menses, will use adequate contraception

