## 7 STUDY EVALUATIONS

### 7.1 STUDY PROCEDURES

The current SARS-CoV-2 pandemic leads to changes from the routine procedures of study visits and to the following regulations: Patients must undergo a SARS-CoV-2 rapid test prior to each study visit (either to bring a test no older than 24 hours or a rapid test will be performed on site). Depending on the SARS-CoV-2 incidence rate and the current operating guidelines, it must be weighed whether the currently prevailing risk of infection for the patient is increased by an on-site visit. This is the case for all patients not fully vaccinated against SARS-CoV-2. For these patients, visits not including study drug administration (weeks 16 through 32) may be replaced by remote (video) visits. SARS-CoV-2 infection of study participants will automatically lead to study drug discontinuation but not necessarily to study termination. Rather, the follow-up phase can be continued once quarantine/COVID-symptoms/SARS-CoV-2 PCR positivity have resolved.

The study-specific procedures for each patient visit at the study site are shown in the following table.

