## 9.2 SAMPLE SIZE DETERMINATION

The primary objective of this exploratory study is to evaluate whether treatment with the anti-CD38 antibody daratumumab is associated with a significant reduction of pathogenic serum anti-dsDNA antibodies in patients with moderate to severe SLE. Results from two patients treated with daratumumab in our institution (compassionate use) resulted in a mean reduction of anti-dsDNA antibodies by 250 IE/ml (SD 121) what corresponds to a reduction of about 50% at 90 days follow-up after first dose of daratumumab. It yields an effect size of 2.1. A sample size of 5 patients is necessary to show a significant reduction in anti-dsDNA antibodies by a two-tailed Wilcoxon signed-ranked test for matched pairs between baseline and the 12-week follow-up visit, assuming a statistical power of 80% and a type one error rate of 5%. We conservatively assume a drop-out rate of 50%. Therefore, a total of 10 patients will be enrolled in this exploratory study. Sample size calculation was performed with G\*Power version 3.1.9.2.

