### 9.3 ANALYSIS SETS

All patients who were enrolled into the study are included in the main analyses. In fact, the primary and secondary outcome measures are analyzed according to the intention-to-treat principle. In addition, a modified intention-to-treat analysis is planned, excluding patients with a dose interruption in case of an adverse event or discontinuation of study treatment for other reasons, such as use of prohibited medication (see section 6.6). A complete case analysis is performed as sensitivity analysis.

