### 9.6 PHARMACODYNAMIC AND BIOMARKER ANALYSES

The number and phenotype of peripheral blood immune cell subsets will be assessed using multicolor flow cytometry. Descriptive statistics will be used to report the biomarker at each assessment. The change in efficacy parameters will be analyzed by linear mixed models.

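### LOCF as the primary rule for missing efficacy outcomes, with no limit by visit or study period, can put the wrong titre at Week 12 and overstate durability to Week 84

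*Protocol*

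**What the plan says.** Protocol section 9.4 gives the rule: "Missing values in primary and secondary outcome measures will be replaced by the last known value of any previous assessment (LOCF principle". It governs the primary analyses and has one exception: "Missing data for safety endpoints will not be replaced". Section 9.3 fixes the population: "All patients who were enrolled into the study are included in the main analyses". The same section adds a complete case analysis, but only as a sensitivity analysis.

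The primary result (section 9.5.1) is the median change in anti-dsDNA titre from baseline to Week 12, with a 95% confidence interval and no confirmatory test. Section 3.2.3 reports most secondary efficacy outcomes by visit, through Week 36 of the core study and then at Weeks 42 to 84 of the long-term extension (LTE). Section 5.3 makes entry to the LTE conditional: "Written consent to the long-term extension of the observational period". On attrition, section 9.2 says "We conservatively assume a drop-out rate of 50" per cent. Section 9.5.2 analyses time to flare and time to next treatment by Kaplan-Meier.

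**The concern.** The trial asks two efficacy questions: has the titre fallen four weeks after dosing stops, and does the effect last? LOCF answers both by assumption for anyone with missing data, because it holds the last value constant.

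The protocol's own background gives no support for a constant titre. Section 2.1.3 reports for another plasma-cell-depleting drug: "Within ten days of the last bortezomib injection, PC numbers significantly increased, accompanied by recurrence of anti-dsDNA antibodies". Section 2.1.4.5 reports that in the two pilot patients given daratumumab, most of the serologic response had appeared three to six weeks after the final infusion. The first suggests that a titre carried from Week 9 would flatter the Week 12 result; the second suggests that it would understate it.

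For durability, a patient who leaves as an SRI-4 or LLDAS responder stays a responder at every later visit. Nothing in sections 9.3 or 9.4 stops a non-entrant's Week 36 value from filling the LTE visits. The study is single-arm and untested, so the estimates and intervals are the whole result.

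**Working it through.** **1. The plan's own figures.** Effect size: 250 / 121 = 2.07, given as 2.1 in section 9.2. A paired test with noncentral t and the asymptotic-efficiency correction for the signed-rank test gives power of 0.74 to 0.75 at n = 4 and 0.90 to 0.91 at n = 5, so 5 is the smallest n with at least 80%. Inflation: 5 / (1 − 0.50) = 10. Both figures reproduce. The planning case therefore has 10 − 5 = 5 of 10 Week 12 titres missing, and carried under section 9.4.

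**2. How many are likely to be missing at Week 12.** Section 9.2 does not say when the 50% falls. Assuming a constant hazard:
- 50% by Week 36: 1 − 0.5^(12/36) = 0.206, about 2.1 of 10.
- 50% by Week 84: 1 − 0.5^(12/84) = 0.094, about 0.9 of 10.

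Five of 10 is the upper planning figure, not the expected number.

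**3. Which titre is carried.** In the section 7.1.1 schedule the last dose is on Day 49 and Week 12 is Day 77, which is 28 days later. The Week 9 titre is on Day 56, 7 days after the last dose. Titres from Weeks 3, 5 and 7 are on treatment.

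**4. Effect on the Week 12 median.** Assume true reductions that are normal with mean 250 and SD 121 IE/ml (section 9.2) in 10 patients. Let each carried value equal a fraction g of that patient's own Week 12 reduction. By simulation (100,000 trials), the expected LOCF median reduction against a true 250 is:

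| g | 2 of 10 carried | 5 of 10 carried |
|---|---|---|
| 0 (baseline carried) | 212 | 57 |
| 0.5 | 219 | 169 |
| 0.8 | 239 | 222 |
| 1.0 | 250 | 250 |
| 1.2 (rebound after Week 9) | 259 | 273 |

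The bias runs either way, depending on g, which is unknown.

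**5. Effect on the interval.** The protocol names no method. As an illustration, take the order-statistic interval for a median. At n = 10 the 2nd to 9th values give coverage 1 − 22/1024 = 97.9%. At n = 5 the minimum to maximum gives 1 − 2/32 = 93.75%. With 5 carried at g = 0.5, the LOCF interval has mean width of about 231 IE/ml, against about 282 for the five observed patients: narrower, yet with higher nominal coverage. At g = 0 it is wider (about 310), so the interval is not always too narrow. The fault is that it treats imputed values as data.

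**6. Durability.** Let a fraction f not enter the LTE, with the same response rates in entrants and non-entrants: p36 at Week 36 and p84 at Week 84. LOCF reports (1 − f) × p84 + f × p36, an excess of f × (p36 − p84). This is positive whenever response wanes. All rates below are assumptions.
- f = 0.5, p36 = 60%, p84 = 30%: 0.5 × 30 + 0.5 × 60 = 45%, against a true 30%.
- f = 0.3, p36 = 70%, p84 = 20% to 40%: 35% to 49%.
- f = 0.5, p36 = 70%, p84 = 20% to 40%: 45% to 55%.

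**The case against.** The other side has several good points.

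- **The rule is not universal.** Safety, which is secondary endpoint 1 and the LTE primary endpoint, is not imputed, and the time-to-event endpoints use Kaplan-Meier. This stands, and limits the point to the remaining efficacy outcomes.
- **The observed data will be shown.** Section 9.3 plans a complete case analysis. That helps, but it leaves the LOCF figure as the headline result.
- **Few Week 12 titres should be missing.** Under section 8.2, stopping drug does not end follow-up. Under section 8.3, withdrawal by decision of sponsor, investigator or participant triggers a visit with the Week 36 (or Week 84) procedures. A zero-change imputation needs a patient with no post-baseline titre at all, so the 57 IE/ml case is remote. However, a termination-visit titre carried to Week 12 still need not be four weeks off drug.
- **LOCF may be conservative at Week 12.** On the pilot time course it could be. The direction is open, which is not a reason to make it primary.
- **LTE carry-forward is not an express rule.** Correct: it follows from reading sections 9.3 and 9.4 literally, and the sponsor may not intend it.

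A reader might infer two further faults that the document does not support. Section 7.1 says "visits not including study drug administration (weeks 16 through 32) may be replaced by remote (video) visits" for patients not fully vaccinated, and one could conclude that titres at those visits are then carried; the section is silent on blood sampling. Section 9.6 says "The change in efficacy parameters will be analyzed by linear mixed models", and one could conclude that imputed values enter those models. Section 9.6 covers pharmacodynamic and biomarker outcomes, which section 3.2.4 lists as additional endpoints, while section 9.4 covers primary and secondary outcomes only.

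**Conclusion.** The point holds and should be fixed. It does not undermine the study, which is exploratory and plans an observed-data sensitivity analysis.

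At Week 12 the rule can replace the defined endpoint with a titre from another time, biasing the median in an unknown direction. The upper planning figure is 5 of 10 patients; about 1 to 2 is more plausible if drop-out is spread over follow-up. It would go too far to say that half the Week 12 titres will be imputed or that the effect is manufactured: the 50% is planning inflation with no stated timing, and the error may run against the drug.

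The case is clearer for durability. Under the literal reading, carry-forward favours the drug whenever response wanes, by f × (p36 − p84): 15 percentage points in the 60%/30% illustration. That size rests on assumed response rates, assumed non-entry and equal rates in entrants and non-entrants; the protocol gives none of these.

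**What to change.** Amend section 9.4, and section 9.5 to match:

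1. Report the Week 12 median change and its interval on observed titres, with the number missing. State the interval's actual coverage, since with five observed values a distribution-free interval cannot exceed 93.75%.
2. Keep LOCF as a sensitivity analysis. A repeated-measures model on log titres may be added in the same role. It should not replace the median change as the primary result, which would change the estimand and rest on strong assumptions in 10 patients.
3. Count missing SRI-4 and LLDAS in the core period as non-response.
4. Report Weeks 42 to 84 as observed in patients who entered the LTE, with the denominator at each visit, and carry nothing forward past Week 36.

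The cost is wording and minor programming; no patient procedure changes. Responder rates and LTE denominators will look less favourable, and the Week 12 interval will usually be wider.

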### 9.5 EFFICACY ANALYSES

#### 9.5.1 PRIMARY ENDPOINT ANALYSIS

The median and interquartile range (25th centile – 75th centile) is reported for anti-dsDNA antibody titers at baseline and at Week 12, i.e. 4 weeks after the last daratumumab injection. The change in between the two assessments is not tested in a confirmatory manner because of the exploratory study design. The median change is reported with its 95% confidence interval.

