| Rationale:                           | Daratumumab has been investigated in several phase III clinical trials in patients with multiple myeloma, a plasma cell malignancy, where it demonstrated efficacy with an acceptable safety profile. It is now intended to evaluate whether daratumumab also provides a clinically significant efficacy in SLE, another disease in which plasma cells have been demonstrated to play a pathogenic role. Previous experiences with the utilization of daratumumab in two patients with SLE indicated that one cycle of 4 weekly daratumumab infusions was associated with significant serologic and clinical responses. |
| Objectives of the core study period: | Primary objective
The primary objective of this study is to evaluate whether treatment with eight weekly subcutaneous injections of daratumumab is associated with a reduction of pathogenic serum anti-dsDNA antibodies in patients with moderate to severe SLE.                                                                                                                                                                                                                                                                                                                                             |

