### 3 OBJECTIVES, ENDPOINTS, AND HYPOTHESIS OF THE STUDY

#### 3.1 OBJECTIVES

##### 3.1.1 PRIMARY OBJECTIVE OF THE CORE STUDY PERIOD

The primary objective of this study is to evaluate whether treatment with eight weekly subcutaneous injections of daratumumab is associated with a significant reduction of pathogenic serum anti-dsDNA antibodies in patients with moderate to severe SLE.

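### The primary objective and the sample size rest on a significance test that the analysis section does not run, and no stated result decides the objective or the condition for the PK assay

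*Protocol*

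**What the plan says.** **Objective.** Protocol 3.1.1 asks whether treatment "is associated with a significant reduction of pathogenic serum anti-dsDNA antibodies in patients with moderate to severe SLE". Section 9.2 repeats this while calling the study exploratory: "The primary objective of this exploratory study is to evaluate whether treatment with the anti-CD38 antibody daratumumab is associated with a significant reduction". Section 3.3 hypothesises a significant decrease. The synopsis states the same objective without the word: treatment "is associated with a reduction of pathogenic serum anti-dsDNA antibodies in patients with moderate to severe SLE".

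**Sizing.** Section 9.2 gives 5 patients as the number needed "to show a significant reduction in anti-dsDNA antibodies by a two-tailed Wilcoxon signed-ranked test for matched pairs between baseline and the 12-week follow-up visit", with 80% power and a 5% type I error rate. Allowing for 50% drop-out gives 10 enrolled. The synopsis sizing paragraph says the same, including the word *significant*.

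**Analysis.** Section 9.5.1 says "The change in between the two assessments is not tested in a confirmatory manner because of the exploratory study design", and then "The median change is reported with its 95% confidence interval". The synopsis likewise excludes a confirmatory test and promises a 95% interval for the median change. Neither place names the interval method.

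**Consequence of the result.** The daratumumab serum concentration is measured only if the primary endpoint is achieved (synopsis additional objectives, 3.1.3, 3.2.4, 7.5 and 9.7). None of these sections says what achieving it means. The endpoint definitions in 3.2.1 and 7.3.1 give only the comparison of Week 12 with baseline.

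**The concern.** An objective worded as a significant reduction calls for a yes-or-no answer, and the sample size is justified by a procedure that gives one. The analysis section excludes that procedure in its confirmatory role and puts no other deciding result in its place. The report could then describe the same data as a significant reduction, or decline to, with nothing in the protocol to settle it.

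Three things are at stake. The power statement describes an analysis that is not planned. The primary objective reads differently in the synopsis and in the body. One later piece of work, the PK assay, is switched on or off by a criterion that nobody has written down. The trial is open-label and uncontrolled (section 4.1), so a criterion fixed in advance is one of the few protections it has.

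**Working it through.** **1. The stated sample size reproduces.** Inputs from 9.2: mean fall 250 IE/ml, SD 121, two-sided 5%, power 80%, drop-out 50%.

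- Effect size: d = 250/121 = 2.07 (stated as 2.1).
- Paired Wilcoxon power by the usual efficiency-adjusted noncentral t: N' = N × ARE, df = N' − 1, noncentrality = d × √N', with ARE = 3/π for normal changes. That the cited software works this way is an assumption.
- N = 4 gives 73.8% and N = 5 gives 90.2%. With the minimum ARE of 0.864 the values are 63.9% and 84.0%. So 5 is the smallest N with at least 80%.
- Enrolled: 5/(1 − 0.5) = 10.

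The arithmetic is as stated, but it is the power of a Wilcoxon test. It also holds only by approximation: with 5 pairs the smallest exact two-sided p-value is 2/2⁵ = 0.0625, so the exact test could not reach 5% with 5 completers.

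**2. The statements side by side.**

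| Place | Significance in the objective? | Deciding procedure |
|---|---|---|
| Synopsis, objective | no | none |
| 3.1.1 and 3.3 | yes | none |
| 9.2 and synopsis sizing | yes | two-tailed Wilcoxon, 5% |
| 9.5.1 and synopsis analysis | no confirmatory test | median change with 95% CI, no decision rule |
| 3.1.3, 3.2.4, 7.5, 9.7 | – | PK assay if *achieved*, undefined |

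No row of the analysis answers the objective as 3.1.1 and 9.2 word it.

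**3. Could the choice of deciding result matter?** Take n = 10 and two candidates.

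- Exact Wilcoxon: a fall is significant if the smaller rank sum is 8 or less (two-sided size 0.0488).
- Exact order-statistic interval for the median: 2nd to 9th ordered change. Coverage is 1 − 2(1 + 10)/1024 = 97.9%; the 3rd to 8th covers 1 − 2(1 + 10 + 45)/1024 = 89.1%. The interval lies below zero only if at least 9 of 10 patients fall.

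Two illustrative data sets (invented, not trial data):

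- Changes −250, −220, −200, −180, −150, −120, −90, −60, +20, +30: Wilcoxon p = 0.0098, but the median interval is (−220, +20).
- The same with the last two replaced by −40 and +300: Wilcoxon p = 0.084, but the median interval is (−220, −40).

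The candidates can therefore disagree in either direction.

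**4. How often?** Simulated trials, n = 10, normal changes. The 95% median interval was built in two standard ways because the protocol does not say which is meant.

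| True standardised fall | Wilcoxon shows a fall | Exact order-statistic CI below 0 | Verdicts differ, exact | Verdicts differ, interpolated |
|---|---|---|---|---|
| 1.0 | 78% | 51% | 28% | 12% |
| 2.07 (planning value) | about 100% | 98% | 1.5% | 0.1% |

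At 1.0 the interpolated interval lies below zero in about 71% of trials. A Hodges-Lehmann interval inverts the Wilcoxon test, so with it the verdicts would agree by construction.

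**5. Is one interval clearly better?** With normal changes the mean widths are 2.00 SD (exact median), 1.55 SD (interpolated median) and 1.43 SD (Hodges-Lehmann). With heavy-tailed changes (t with 3 df) the interpolated median interval is narrower than Hodges-Lehmann, 1.11 against 1.27 SD. The ranking depends on the method and on the distribution.

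**The case against.** The strongest defence is that a ten-patient proof-of-concept study may properly estimate rather than test. Section 9.5.1 names one primary analysis and says why there is no confirmatory test, and a sizing section is not an analysis plan. The interval method is the kind of detail a statistical analysis plan settles. The protocol also uses *significant* loosely elsewhere: section 2.1.4.5 applies it to results in two patients.

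Much of this stands. A reader might infer that the protocol contains two rival analyses and lets the authors pick the winner. It does not: citing 9.2 to claim significance would contradict 9.5.1. Nor is all testing forbidden, since only confirmatory testing is excluded. A reader might also take the 28% disagreement as a property of the plan. It rests on an assumed interval method and on an effect about half the planning value.

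What the defence does not remove is the conflict within the protocol. Sections 3.1.1 and 9.2 state the objective with a significance claim, the synopsis objective states it without one, and no result is named as deciding it. Choosing an interval method in an analysis plan would not reconcile those sections. The condition on the PK assay is a yes-or-no decision that the protocol itself creates, and an exploratory label does not define it.

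**Conclusion.** The point holds as a mismatch between objective, sizing and primary analysis, together with an undefined success condition for the PK assay. The quoted 80% power does not describe the planned analysis. It should be corrected before the data are analysed.

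The numerical stake is modest at the protocol's own assumptions. At the planning effect of 2.07 the candidate verdicts differ in about 1.5% of trials or fewer. It grows to about 12% to 28% at an effect of 1.0, which cannot be dismissed because the planning value comes from two patients. These figures assume 10 analysed patients, normal changes, and an order-statistic interval for the median, exact or interpolated.

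It would be tempting to conclude that the median interval is the wrong choice and that a Hodges-Lehmann interval must replace it. The evidence does not support that. Hodges-Lehmann matches the sizing test, but it is not uniformly more precise, and it estimates the median only if the changes are roughly symmetric.

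**What to change.** Choose one of two options and apply it in 3.1.1, 3.3, 9.2, 9.5.1 and the synopsis (objective, sizing and analysis paragraphs).

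- **(a) Estimation.** Delete *significant* from the objective and hypothesis. Present the Wilcoxon calculation as a planning aid only, and say that it is not the power of the primary analysis.
- **(b) Exploratory decision.** Keep *significant*, and name one deciding result before analysis: for example, that the pre-named 95% interval for the change from baseline to Week 12 lies wholly below zero. Name the interval method. A Hodges-Lehmann interval is acceptable, and so is a stated median interval. Say what applies if only 5 patients are evaluable: the widest exact order-statistic interval then covers only 1 − 2/2⁵ = 93.75%, and the exact Wilcoxon test cannot reach 5%.

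Under either option, define *primary endpoint achieved* for the PK assay in 3.1.3, 3.2.4, 7.5, 9.7 and the synopsis by that same result. Under (a) this means stating which estimate or interval triggers the assay.

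The cost is wording in these sections. No patients, visits or samples are added.
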